#### 3. Invasive Electroencephalograghy (iEEG)

iEEG recordings will be obtained from patients with pharmacologically resistant epilepsy undergoing invasive electrophysiological monitoring at the Comprehensive Epilepsy Center at New York University Langone Health Center, Brigham and Women’s Hospital, Children’s Hospital Boston, and Johns Hopkins Medical School and University of Wisconsin School of Medicine and Public Health.

*Electrophysiological data acquisition*. Brain activity will be recorded from intracranially implanted subdural platinum-iridium electrodes embedded in SILASTIC sheets (2.3 mm diameter contacts, Ad-Tech Medical Instrument and PMT Corporation). The decision to implant, electrode targeting, and the duration of invasive monitoring will be solely determined on clinical grounds and without reference to this or any other study. Macroelectrodes will be arranged as grid arrays (8 × 8 contacts, 10 or 5 mm center-to-center spacing), linear strips (1 × 8/12 contacts), or depth electrodes (1 × 8/12 contacts), or a combination thereof. Subdural electrodes will cover extensive portions of lateral and medial frontal, parietal, occipital, and temporal cortex of the left and/or right hemisphere. Recordings from grid, strip and depth electrode arrays will be made using a Natus Quantum (Pleasonton, CA), Xltek (San Carlos, CA) or a Blackrock system (Salt Lake City, UT) amplifier. Recordings are obtained continuously during the patients’ stay in the hospital. All data will be stored with stimulus and timing markers permitting offline synchronization.

*Surface reconstruction and electrode localization*. Pre-surgical T1-weighted MRIs (no electrodes) and post-surgical CT scan (with electrodes) will be acquired for each patient and used to determine electrode locations, following the general methodology of Yang et al. (2012) or Dale et al. (1999) [62, 63] using the Freesurfer package (HU). For NYU, skull-stripped post-surgical CT images will be linearly co-registered to the pre-surgical MRI. Electrode locations will be extracted using the co-registered CT images, and projected to the reconstructed brain surface, generally following the procedure described by Yang and colleagues. MRI images will be nonlinearly registered to an MNI-152 template. The same transformation will be applied to the co-registered CT image in order to map the extracted electrode coordinates in Montreal Neurological Institute (MNI) space. A three-dimensional reconstruction of each patient’s brain will be computed using FreeSurfer (http://surfer.nmr.mgh.harvard.edu).

At Harvard, the pial surface of each subject will be reconstructed using Freesurfer from the presurgical MRI. The Freesurfer function “recon-all” will be used, following the fully-automated directive (“-autorecon-all” flag). The CT images of the implanted electrodes will be localized to the MRI reconstruction using the iELVis package (Groppe et al., 2017) [64]. CT gantry tilt will be corrected using the dcm2niix package from www.nitrc.org. Electrode grid and strip orientation will be identified in the CT scan based on pre-surgical sketches and platinum marker guides (Ad-Tech, Racine, WI, USA). The electrode locations will then be summarized by mapping them onto one of 36 brain areas based on the parcellation of the Desikan-Killiany atlas (Desikan et al., 2006) [65] using the “recon-all” function in Freesurfer.

*Behavioral setup*. The experiment will be controlled and the stimuli will be presented on a Dell Precision 5540 laptop, with 15.6" Ultrasharp screen (screen size 357.27 x 235.47 mm2; resolution 1920x1080) running on Windows 10. The laptop will be positioned at 55–65 cm from the patient. Audio will be presented through loudspeakers.

*Eye tracker*. Eye-tracking data will be collected throughout the duration of the experiment using a Tobii-4C eye-tracker (New York University) and EyeLink 1000 Plus Camera (Harvard University and University of Wisconsin). Thirteen-point calibration will be performed several times during the experiment. The calibration will be performed at the beginning of the experiment, and recalibrated if necessary to meet precision requirements at the beginning of each mini-block. Pupil size and corneal reflection data will be collected at a sampling rate of 90Hz at New York University and at a sampling rate of 500Hz at Harvard university and University of Wisconsin. Only one eye will be recorded as determined by ocular dominance. The experiment will not be influenced by the Eye-tracking recording.

### Data management and sharing plan

Our plan to share neuroimaging, electrophysiological, behavioral and eye tracking data, and our management of intellectual property will be in accordance with the policies and guidelines of our institutions and NIH. All investigators involved in this project will adhere to NIH’s Data Sharing Policy and Implementation Guidance of March 5, 2003 and NIH Grants Policy on Sharing of Unique Research Resources including the “Sharing of Biomedical Research Resources: Principles and Guidelines for Recipients of NIH Grants and Contracts” issued in December, 1999.

The investigators acknowledge their willingness to share data and materials stemming from this project in order to maximize impact and to accelerate discoveries to understand consciousness and its neural substrates. As soon as data have been acquired, data will be uploaded to the central cloud server of the project, hereby making it immediately available to all members of the team. Throughout the course of the 3 years that the project is expected to last, data will be shared with local colleagues at seminars and talks, and with the scientific community at large by posters and presentations at local, regional, national and international scientific meetings. Finally, data will be presented by publication to the widest audience possible.

Following publication of the primary adversarial collaboration manuscript, the research data will be made available to the scientific community through public repositories.

Specifically, as part of our resource sharing plan, we will develop a website on which the following resources pertaining to this proposal will be made publicly available:

Any Matlab (binaries)/ Python code used to analyze or pre-process the dataAny MRI pulse sequences (binaries) used to acquire the dataAll (de-identified and PHI removed) MRI, neurophysiological, eye tracking and behavioral data adhering to the FAIR principle. Specifically, raw data will be shared both in native formal and also in Brain Imaging Data Structure BIDS format (http://bids.neuroimaging.io). All metadata will be made available.Any peer-reviewed article (depending on journal restrictions)Any experimental code

In order to access or download files containing behavioral, eye tracking, neurophysiological or MRI data, users will have to register. As they register, they will agree to restrictions against attempting to identify study participants, restrictions on redistribution of the data to third parties, and to properly acknowledge the data resource. The neurophysiological recordings (clinical iEEG and experimental electrodes), relevant task data, electrode coordinates in MNI space and essential, de-identified clinical data using NINDS Common Data Elements (age, sex, duration of epilepsy, epilepsy etiology, preoperative imaging findings) and schematics of seizure onset areas will also be made available. Data will be converted to shareable data formats (BIDS). Machine-readable annotation of the task and Matlab/Python scripts to synchronize data streams will be included. All data will be reviewed prior to upload to ensure they contain no PHI. Data will be stripped of voice recordings and be HIPAA compliant. Data will be made available to the research community by sharing them through different steps in the analysis pipeline. We will share un-processed (DICOM), minimally preprocessed (NIFTI format) and final processed (NIFTI format) data. All custom code and analysis pipeline will also be shared.

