**Fig 1 pone.0268577.g001:**
[figure not shown]
Core predictions, analyses, and potential results for the two experiments. For each theory (white circles), the core predictions (white rectangles) and possible outcomes (colored rectangles) are summarized. Green squares denote positive outcomes, red ones denote negative outcomes, and yellow squares denote negative outcomes that are less conclusive, as they might stem from limitations of the methods or analyses. On the right, we conclude how combinations of results would reflect on the theories. Note that some predictions require time-resolved measures (M-EEG, iEEG), while others can be tested with all three techniques. PFC refers to Prefrontal cortex; RSA refers to representational similarity analysis [RSA; 48]; IT refers to inferotemporal cortex; LOC refers to lateral occipital cortex; V1 refers to primary visual cortex.

To test the predictions, we will acquire fMRI and M-EEG data in neurotypical adults and invasive electrophysiological measures, iEEG, in patients with refractory epilepsy for both experiments. This combination of methods will provide the best set of tests for the hypotheses, considering acknowledged limitations of instruments available for human neuroscience. To minimize implicit bias, researchers without prior commitment to either theory will acquire and analyze the data in consultation with expert advisors. All data will be collected in duplicate, in two separate laboratories with two independent samples (a minimum of 50 subjects will be collected for each experiment for fMRI and M-EEG; 25 subjects will be collected for each experiment for iEEG for a total of 250 collected datasets in each experiment. Whenever feasible, subjects will participate in both experiments to allow for generalization across experiments (if not possible, additional subjects will be recruited).

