#### Analysis approach

We have preregistered the experimental design, predictions and expected outcomes for each theory, while leaving open the specification of the analysis methods. This will allow for the development of analyses while still committing to a preregistered protocol. The data will be split into two halves, so the first-half is used to optimize the analysis methods (phase 2, analysis optimization), with the aid of expert advisors. Then, analysis routines and all specific details will be locked, the preregistration will be amended, and the second half of the data will be used for replication (phase 3, replication). Thus, in accordance with our plan, the current protocol includes a higher-level description of the analyses and explicit, fleshed-out predictions, but does not include all of the analysis details.

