The project is tripartite. At the time of submission of this study protocol, phase 1 is approximately halfway complete. In **phase 1**, all data will be acquired by theory neutral teams. To ensure replicability of the results, the entire dataset will be split into two halves, each with an equal mixture of data from each of the two labs for each recording technique (half of the participants tested in both labs). In **phase 2**, after evaluating data quality (see OSF preregistration), the first half of the data will be used for developing analysis tools (optimization of methods). The purpose of **phase 2** is to define the best analysis practices and to agree upon, in consultation with expert advisors, the detailed analysis protocols that will be preregistered in the final, unchangeable version of the preregistration. In our original protocol, phase 1 and phase 2 were planned to be conducted successively, yet due to delays in data acquisition caused by the COVID-19 pandemic of 2020–2021, now phase 1 and phase 2 will overlap. In **phase 3**, the replication phase, the second half of the data will be analyzed using these preregistered, agreed upon protocols, thereby allowing an in-house replication of the results obtained in phase 2. Data will be analyzed by the acquiring laboratories, a data analysis team composed of the two theory leaders, the center PIs (the three co-first authors leading this project), and a method-experts advisory panel. All data, meta-data, stimulation protocols, and analysis pipelines will be publicly released upon the publication of the final results via a combination of documents in OSF, raw data, processed data and analysis code, and protocol instructions and specifications in SLAB (data management and sharing plan are detailed below).

### Experiment 1

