## Discussion

We have embarked upon an ambitious and large-scale endeavor involving a dozen laboratories in three continents using an open science and adversarial collaborative process. The field has already made substantial progress with a myriad of individual studies [e.g., 18, 66], but systematic tests of the theories’ predictions in a large-scale, multimodal design have not yet been attempted. The present study protocol results from the first stage of this project–finding agreement among scientists with conflicting views for two meticulously planned studies, the associated instruments and analysis tools, as well as funding for such a costly enterprise. The two studies were extensively piloted (on more than 250 subjects; see OSF page). Those pilots established the adequacy of the experiments for yielding the desired behavioral and eye movement patterns, and served to rule out potential confounds. We are now in the process of collecting 500 datasets (250 subjects x 2 studies) using our chosen techniques—fMRI, M-EEG and iEEG—in phase 1 (Fig 4). This will complete the data acquisition phase. The first half of this massive data volume, that will reside in a secure server during the completion of the project, will be used to test the specific and detailed hypotheses described above, in phase 2. All aspects of the processing pipeline will be finalized and frozen before proceeding to the analysis of the second half of the data in phase 3, to assure the generalizability of the final results. These will then be published in platform papers, with all data, meta-data, stimulation protocols, and analysis code made freely available to anyone for further analysis or extension experiments.

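### The replication half is held out only by order of analysis: it is open to the whole team, theory leaders included, before the pipeline is locked

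*Protocol article*

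**What the plan says.** All references are to the protocol article.

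- **Split and lock.** Status and timeline: "the entire dataset will be split into two halves, each with an equal mixture of data from each of the two labs". Analysis approach: after optimization on the first half, "analysis routines and all specific details will be locked, the preregistration will be amended, and the second half of the data will be used" in the replication phase. The Discussion repeats that the pipeline is frozen before the second half is analyzed.
- **Access.** Data management and sharing plan: as soon as they are acquired, "data will be uploaded to the central cloud server of the project, hereby making it immediately available to all members of the team". The same section foresees sharing at seminars, talks and scientific meetings while the project runs. Neither statement distinguishes the two halves.
- **Who analyzes.** Overall rationale for testing the competing predictions (text after Fig 1): to limit implicit bias, "researchers without prior commitment to either theory will acquire and analyze the data". Status and timeline: the analysts are the acquiring laboratories and "a data analysis team composed of the two theory leaders", together with the center PIs and a panel of method experts.
- **Role of the first half.** Analysis approach and Status and timeline give it to method optimization. The Discussion says that it "will be used to test the specific and detailed hypotheses described above, in phase 2".
- **What is still open before the lock.** Multivariate decoding (Experiment 1) lists seven candidate decoders. The M-EEG section leaves the source-localization method open (beamforming or minimum-norm estimation) and lists two inter-subject alignment methods to compare.

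**The concern.** The article deliberately leaves the analysis methods open until the lock, and the second half is the main check on that freedom. A replication is independent only if nothing learned from its data shaped the pipeline. The stated access rule lets the people who choose the pipeline open the replication data before the choice is final. Some of them have a stake in the result, and the article's impartiality statement does not fit their place on the analysis team.

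If second-half results were known during tuning, even informally or through an interim talk, the second half would partly repeat the selection instead of testing it. The wording in the Discussion adds a smaller problem. Tests run on the half used for tuning are optimistic, so the reader needs to know which half carries the confirmatory reading.

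**Working it through.** **1. Does any statement close the second half before the lock?**

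| Statement | What it controls |
|---|---|
| Analysis approach; Status and timeline; Discussion | Order of analysis: tune on the first half, lock, then analyze the second |
| Multivariate decoding | Which half is used to select the decoder: the first |
| Data management and sharing plan | Access: all data, all team members, from acquisition |
| Discussion, secure server | Storage; not described as closed to the team |

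The first two rows are rules of conduct. The only rule on access within the team is the third, and it is unqualified. No statement bars access to second-half files before the lock.

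**2. Size, if access were used.** The plan gives no figure on this point (its power statement does not bear on it), so there is none to reproduce. The inputs are:

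- 7 decoders, from Multivariate decoding.
- One-sided test at 5%, critical value 1.645. This is an assumption; the article states no level.
- Common correlation r between decoders of 0, 0.5, 0.8 or 0.95. This is an assumption; decoders run on the same data are likely to be highly correlated.

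Under the null, decoder k (k = 1 to 7) in half h has the statistic

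Z(h,k) = √r · U(h) + √(1 − r) · E(h,k),

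with U and E independent standard normal and the two halves independent. A false positive is Z(2,k*) > 1.645 for the chosen decoder k*. Two selection rules were simulated, with 400,000 runs each:

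- Sealed: k* maximizes Z(1,k).
- Both halves inform the choice, equally weighted: k* maximizes Z(1,k) + Z(2,k).

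| r | Sealed | Both halves inform the choice |
|---|---|---|
| 0 | 0.050 | 0.203 |
| 0.5 | 0.049 | 0.146 |
| 0.8 | 0.050 | 0.105 |
| 0.95 | 0.050 | 0.075 |

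Simulation error is small: at 0.20 the standard error is √(0.20 × 0.80 / 400,000) ≈ 0.0006. The sealed rate stays at 5% whatever the correlation. The other column falls towards 5% as the decoders become more alike, so its lower rows are the more realistic ones. Source and alignment options are not included.

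**The case against.** The strongest defense is that the plan does hold the second half out. Three sections commit to tuning on the first half, freezing the pipeline in a final preregistration, and only then analyzing the second. Files on a server are not an analysis, and ongoing quality checks need some central access. The full preregistration is not shown and may contain access controls. Both opposing theory leaders sit on the team, so each can check the other.

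Much of this stands, and it rules out several stronger readings that a reader might infer:

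- *That the second half is not held out at all.* The promised order of analysis contradicts this.
- *That the pandemic change created the exposure.* The article says "now phase 1 and phase 2 will overlap". Under the planned successive order, all second-half data would have been acquired before tuning began. Overlap can only reduce what is available during tuning.
- *That the false-positive rate would be 30%, 20% or 13% (r = 0, 0.5, 0.8).* Those rates arise if the best of seven decoders is picked on the second half itself; for independent decoders, 1 − 0.95^7 = 0.302. The plan assigns the selection to the first half.
- *That theory leaders must be kept out of phase 3.* Their presence is a governance choice with arguments on both sides in an adversarial collaboration. The documents show only that two statements on who analyzes do not agree.

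What the defense does not answer is the access sentence itself. It is a stated rule without qualification, so the point does not rest on detail that an article leaves out. If the preregistration restricts access, the article misstates it and still needs correcting.

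**Conclusion.** The point holds in a limited form. The second half is held out by intention and order of analysis, but it is not sealed: the stated rule opens it to everyone, including the theory leaders, before the lock. This weakens the claim of an independent replication. It does not show bias, because nothing in the article indicates that the access would be used.

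The illustrative exposure is a second-half false-positive rate of about 7% to 20% against 5% if sealed. It assumes a one-sided 5% level, a common correlation of 0.95 to 0, and a choice that weights both halves equally. Separately, the article is inconsistent on who analyzes the data, and its Discussion blurs the optimization role of the first half.

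**What to change.** 1. Amend Data management and sharing plan. Set half membership by a seeded list within laboratory and modality. Until the final preregistration is frozen, limit central-server access to second-half neural data to the data manager and the data monitoring team. Acquiring laboratories necessarily hold their own raw files; state that they do not analyze them for the hypotheses before that point.
2. In the same section, limit presentations before the lock to first-half data.
3. Reconcile the impartiality statement after Fig 1 with the analysis team described in Status and timeline, so that the article says once who analyzes the data.
4. Reword the Discussion so that first-half results are labelled as optimization and the confirmatory reading rests on the second half.

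The cost is server permissions, a list and some wording, with no added participants or recordings. The downside is that laboratories and theory leaders wait longer for second-half data. The change should come soon: acquisition was about half complete when the article was submitted, and restricting access later cannot undo access already given.

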## Discussion

We have embarked upon an ambitious and large-scale endeavor involving a dozen laboratories in three continents using an open science and adversarial collaborative process. The field has already made substantial progress with a myriad of individual studies [e.g., 18, 66], but systematic tests of the theories’ predictions in a large-scale, multimodal design have not yet been attempted. The present study protocol results from the first stage of this project–finding agreement among scientists with conflicting views for two meticulously planned studies, the associated instruments and analysis tools, as well as funding for such a costly enterprise. The two studies were extensively piloted (on more than 250 subjects; see OSF page). Those pilots established the adequacy of the experiments for yielding the desired behavioral and eye movement patterns, and served to rule out potential confounds. We are now in the process of collecting 500 datasets (250 subjects x 2 studies) using our chosen techniques—fMRI, M-EEG and iEEG—in phase 1 (Fig 4). This will complete the data acquisition phase. The first half of this massive data volume, that will reside in a secure server during the completion of the project, will be used to test the specific and detailed hypotheses described above, in phase 2. All aspects of the processing pipeline will be finalized and frozen before proceeding to the analysis of the second half of the data in phase 3, to assure the generalizability of the final results. These will then be published in platform papers, with all data, meta-data, stimulation protocols, and analysis code made freely available to anyone for further analysis or extension experiments.

